#### Economic evaluation

A client record form (see section on Outcome Measures) has been developed for DBT therapists to track detailed information about service utilisation and resource use by DBT patients. Effectiveness outcome measures (e.g. EQ-5D-5 L and BDI-II) will also be used to inform the economic evaluation.

### Time point for each outcome

#### Effectiveness evaluation time points

There will be different time points for each sample in this study as the treatment length for adult and adolescent patients is different.

For **adult** patients, the treatment length is 12 months in duration, so there will be four time points for assessment of outcome: baseline (during the week prior to the patients’ first group skills training session), 6 months after baseline (end of module 3), 12 months after baseline (end of programme), and 18 months after baseline (6 months after programme completion).

For **adolescent** patients, the treatment length is 16 weeks in duration, so there will be three time points for assessment of outcome: baseline (during the week prior to the patients’ first group skills training session), 16 weeks after baseline (end of programme), and 32 weeks after baseline (16 weeks after programme completion).

#### Implementation evaluation time points

The quantity of the implementation is monitored weekly through recording of individual therapy and group skills weekly attendance logs completed by the DBT therapists at each site.

The quality of the implementation is measured through the PETQ which will be administered to team leaders for completion two years after teams complete Intensive Training Part I. DBT therapists’ adherence is assessed on an ongoing basis through expert supervision. To assess participant’s experience of the DBT programme, a survey is administered at time points 2, 3 and 4 for adults (alongside self-report outcome measures) and time points 2 and 3 for adolescents (alongside self-report outcome measures).

The experience of the coordinated implementation will be measured by administering surveys to therapists at three time points: prior to attending Intensive Training Part I, 6 months after teams begin delivery of their first DBT programme, and 2 years following Intensive Training Part I.

#### Economic evaluation time points

For **adult** patients, the treatment length is 12 months in duration, so there will be four time points for assessment of outcome: baseline (pertaining to 6 months before the start of the programme), end of module 3 (pertaining to the first 6 months of the programme), end of programme (pertaining to the second 6 months of the programme), and 6 months after programme completion (pertaining to the 6 months following completion of the programme).

For adolescent patients, the treatment length is 16 weeks in duration, so there will be three time points for assessment of outcome: baseline (pertaining to 16 weeks before the start of the programme), end of programme (pertaining to the 16 weeks of the programme), and 32 weeks after baseline (pertaining to the 16 weeks following completion of the programme).

### Sample size

It is anticipated that there will be a total of 442 participants across 16 sites in this research study over a four year period. Of the 312, it is estimated that 120 will be adults with a primary diagnosis of BPD attending Adult Mental Health Services across eight study sites. It is estimated that 96 participants will be adolescents with emotional and behavioural dysregulation (emerging borderline personality presentations) across eight study sites. As the adolescent’s caregiver also attends the skills training sessions, there will also be up to 96 parent/guardian participants. All DBT therapists (approximately 130 clinicians) who train as part of the National DBT Project, Ireland will be invited to participate in the research study.

The power calculation is based on the aim of identifying if the intervention is effective across multiple sites as part of a coordinated national implementation with adults and adolescents. It was decided to use a medium effect size of 0.5 according to Cohen [54] for the power calculation with an alpha level of 0.05. The primary outcome measure chosen for the power calculation is the Borderline Symptoms Checklist [55]. With an anticipated sample size of eight clusters per adult group with 15 patients per cluster, and an intracluster correlation coefficient of 0.01, the power to detect change over time is 92%. With an anticipated sample size of eight clusters per adolescent group with 12 patients per cluster, and an intracluster correlation coefficient of 0.01, the power to detect change over time is 86% [56].

### Recruitment/procedure

Newly established teams who train as part of the National DBT Project, Ireland will be requested to inform the researchers of the start date of their DBT programme. All individuals who partake in the DBT programme at each of the 16 sites between February 2014 and February 2016 will be invited to participate in the study. A group data collection session will take place at each time-point at each of the study sites where a member of the research team will facilitate data collection. Data collection will be scheduled in advance with the DBT team at each location. It is anticipated that this will take place at the beginning of the first skills training session that is delivered as part of the intervention. Prior to visiting each site, each DBT team will be provided with Participant Information Leaflets to distribute to patients to orientate them towards the research study. When the researcher attends for data collection, patients will have had time to read the Participant Information Leaflet and will have an opportunity to ask any questions regarding the research study. It will be outlined that while participation in the study is confidential, there is a limit to confidentiality. In order to maintain safety of patients, the researchers will conduct a risk assessment following data collection at each site, the results of which are communicated to the DBT therapist(s) present. Participants who are unable to attend the group data collection session but who have agreed to participate in the study will be asked to complete the battery of measures at their next individual therapy session. These participants will sign the consent form, complete the measures and place the completed measures in a sealed envelope to be collected by the research team. In such cases, the protocol outlines that DBT therapists will review with the patient, only their answers to the risk assessment items, prior to securely storing the completed measures.

For follow-up data collection, participants will be invited to attend a group data collection session with a member of the research team, complete measures with their DBT therapist or complete measures at home in which case, measures will be posted directly to them by the research team. If participants choose to complete the measures at home, participants will first be asked to provide consent for their local General Practitioner to be contacted should self-harm or suicide risk be identified upon completion of the measures.

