**Methods/ design:**

This study takes the form of a quasi-experimental design. Individuals attending community mental health services who meet criteria for participation in the DBT programme will be allocated to the intervention group. Individuals who live in areas in Ireland where DBT is not yet available, and individuals who choose not to participate in the intervention, will be invited to participate in a treatment-as-usual comparison group. Self-report clinical measures and health service use questionnaires for DBT participants (and parent/guardians as appropriate) will be administered at pre-, mid- and post-intervention, as well as follow-up for participants who complete the intervention. Survey and interview data for DBT therapists will be gathered at three time points: prior to DBT training, 6 months after teams begin delivery of the intervention, and 2 years following training completion.

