### Data analysis

T tests and analyses of variance will be used to assess potential baseline difference in the outcome measures. Linear mixed-effects models will be used to estimate change utilising data available from participants at all time points. These models may be adjusted for clustering in the data due to repeated measures on the same individuals and due to the intervention being delivered across multiple sites.

Content analyses will be carried out on the survey data provided by DBT therapists which will inform the implementation evaluation.

An economic evaluation will be performed to assess the cost-effectiveness of DBT versus treatment-as-usual for the treatment of adults with BPD who engage in self-harm. The cost-effectiveness analysis will compare the relative costs and outcomes (effects) of the DBT intervention. All relevant costs from the perspective of the health care provider will be identified, measured and valued. Direct health service use will be measured by means of a resource use questionnaire. The relevant health effects will be measured in natural health units using recognised scales, for example, the Beck Depression Inventory. In addition, Quality Adjusted Life Years (QALY) will be calculated with the EQ-5D-5 L utility scores. An incremental Cost Effectiveness Ratio (ICER) will be calculated comparing the relative costs and outcomes. The economic evaluation will be conducted in line with the eight-step framework put forward by Drummond et al. [57].

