### Strengths and limitations

As this study is carried out in a real-world setting, DBT therapists do not have dedicated time to devote to research related tasks, as would be the case in a clinical research trial. Therapists are therefore participating in a voluntary capacity in addition to daily routine and regular professional practice. Given the nature of this comprehensive evaluation, it is anticipated that full compliance with the data collection protocol may not always be possible with competing clinical demands. In an effort to offset this risk, each team will be supported by a member of the coordinating team who will provide guidance and assistance with the research evaluation where possible. In addition, in real-world settings, therapists have a mixed qualification and skill set in relation to research related tasks in contrast to those specifically recruited to support clinical research trials.

One of the strengths of this study is that a dedicated research team has been recruited to coordinate and support this multi-site research evaluation. This was done in an effort to reduce experimenter bias which may be present if clinicians who are working with patients conduct data collection. It is anticipated that having a dedicated research team will also increase the reliability and quality of data collection at agreed time points, and will allow for follow-up data collection to maximise dataset completeness. Having a researcher assigned to each team who will support clinicians during the process of the study will also potentially increase response rates and dataset completeness. Feedback will be provided to each participating service and updates will be provided regarding recruitment status on a regular basis by the research team. At the end of the study, summary reports of the results for each individual site, in addition to the pooled data analysis, will be provided to each team to provide feedback to clinicians and aid service planning. The outlined difficulties with regard to real-world research needs to be managed if researchers and clinicians are to work towards increasing external validity i.e. the effectiveness of an intervention in a publicly funded health system implemented in a manner that is sustainable over time.

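### As worded, mid- and post-intervention self-report collection leans on staying in DBT, and nothing says that patients who stop are still approached at 6 months, 12 months or 16 weeks

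*Protocol article*

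**What the plan says.** All places are in the protocol article.

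- **Abstract, Methods/design.** Self-report measures "will be administered at pre-, mid- and post-intervention, as well as follow-up for participants who complete the intervention". Follow-up is named apart from the mid and post occasions and is tied to completing DBT.
- **Recruitment/procedure, general rule.** "A group data collection session will take place at each time-point at each of the study sites". A member of the research team runs the session, and it is scheduled with the local DBT team. The section anticipates that "this will take place at the beginning of the first skills training session that is delivered as part of the intervention".
- **Recruitment/procedure, fallback.** Patients who agreed to take part but cannot attend the group session "will be asked to complete the battery of measures at their next individual therapy session". The next sentence reads: "These participants will sign the consent form, complete the measures and place the completed measures in a sealed envelope".
- **Recruitment/procedure, follow-up paragraph.** For follow-up data collection, patients may attend a group session, complete the measures with their DBT therapist, or "complete measures at home in which case, measures will be posted directly to them by the research team". Those who choose home first consent to contact with their general practitioner if risk is identified.
- **Time point for each outcome.** Adults are assessed at baseline and at 6, 12 and 18 months; adolescents at baseline and at 16 and 32 weeks. The on-programme occasions are labelled by stage of the programme as well as by calendar time.
- **Data analysis.** "Linear mixed-effects models will be used to estimate change utilising data available from participants at all time points".
- **Ethical principles.** Taking part in the research is a choice separate from treatment, so stopping DBT is not the same as withdrawing from the study.

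**The concern.** The study asks whether DBT works when delivered in routine public services. That calls for outcomes on everyone who starts, including those who stop. Non-attendance is foreseen, since attendance is itself listed among the primary outcomes.

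The one route that clearly does not depend on being in treatment is home completion by post. If follow-up in the Recruitment/procedure section means what it means in the abstract, that route does not reach the 6-month, 12-month or 16-week assessments. The routes that remain are a session at the DBT site arranged with the DBT team, the next therapy session, or the DBT therapist. All of them favour patients still in the programme.

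At stake are the patient-completed outcomes, including the Borderline Symptoms Checklist on which the study is powered. If patients who stop are missed and fare worse than their recorded data would predict, the estimated change is too favourable.

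**Working it through.** **1. Which occasions does the postal route cover?**

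| Source | Sense of follow-up | Consequence for 6 months, 12 months and 16 weeks |
|---|---|---|
| Abstract | A stage after mid and post, completers only | Postal route not offered |
| Recruitment/procedure | Not defined; one option is completion with the DBT therapist | Either reading possible |
| Strengths and limitations: a dedicated team "will allow for follow-up data collection to maximise dataset completeness" | Broad, filling gaps in the data | Postal route may be offered |

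The uses do not agree, and under none of them is there a statement that patients who have stopped DBT are approached. By contrast, the section on parents and guardians does give a retention rule for a different case: an adolescent stays in the study when the parent does not attend.

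**2. The plan's own power figures.** Inputs from Sample size: effect 0.5, alpha 0.05, intracluster correlation 0.01, and 8 clusters of 15 adults or 12 adolescents. The sidedness of alpha is not stated.

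- Design effect 1 + (m − 1) × 0.01: adults 1.14, adolescents 1.11.
- Effective n per group: 120 / 1.14 = 105.3; 96 / 1.11 = 86.5.
- Two-group comparison, two-sided, noncentral t with 2 × (8 − 1) = 14 degrees of freedom: 92.1% and 86.3%.

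The stated 92% and 86% are reproduced and are not in dispute here.

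**3. Possible bias.** The documents give neither a dropout rate nor an outcome difference, so both are assumptions: a proportion p = 20% to 40% stops and is not assessed, and δ = 0.3 to 0.5 SD is the shortfall in their outcomes that observed data do not explain.

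- If the mean for patients who stay (or the model's prediction for all) is S, the true mean improvement over all starters is (1 − p) × S + p × (S − δ) = S − p × δ. The overstatement is p × δ.
- Low end: 0.2 × 0.3 = 0.06 SD, and 0.06 / 0.5 = 12% of the planned effect.
- High end: 0.4 × 0.5 = 0.20 SD, and 0.20 / 0.5 = 40%.
- Patients who stop: 24 to 48 of 120 adults (0.2 and 0.4 × 120), and about 19 to 38 of 96 adolescents (0.2 and 0.4 × 96).

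The range is an upper bound for each pair of assumptions, because it supposes that nobody who stops is ever assessed at that point. It is smaller for adults who stop after month 6, since their 6-month value informs the model. An adolescent who stops before week 16, or an adult who stops before month 6, could leave baseline alone to predict from.

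**4. Possible loss of power.** With the formula of step 2 and the same assumed 20% to 40% loss, spread evenly over clusters, adult power falls from 92% to 86% and 77%, and adolescent power from 86% to 79% and 68%. This is secondary; the main risk is bias.

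**The case against.** A reader might infer that patients who stop DBT have no route at all to give mid- or post-intervention data. The article does not support that. The group session at each time point is run by the research team and is not restricted to patients still in DBT. The link to a skills session is stated only for the first one. The therapy-session fallback is described together with signing consent, so it shows how baseline is handled, not how later visits are. The postal route may be meant for all post-baseline collection: the therapist option in the same sentence suits patients still in treatment, and the limitations section uses follow-up broadly.

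A reader might also infer that the analysis is restricted to patients on treatment, or that a mixed model does nothing about the missing values. Neither follows. The Data analysis section uses whatever data are available and sets no on-treatment condition. A likelihood-based model also removes the part of the bias that baseline and, for adults, 6-month values predict. Outcomes that therapists enter on the client record form do not use this collection route.

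Finally, this is a condensed article, and tracing patients who stop treatment could be left to the full protocol. That would answer a complaint about mere silence. It does not answer this point entirely, because the article itself states who is followed up and by which routes, and those statements pull in different directions.

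**Conclusion.** The point holds as a weakness in how collection is specified, not as proof that a route is absent. As worded, the mid and post assessments lean on staying in DBT, the clearly treatment-independent route is attached to a stage that the abstract limits to completers, and continued assessment after stopping DBT is nowhere promised.

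The overstatement is at most about 0.06 to 0.20 SD, or 12% to 40% of the planned effect of 0.5. This is illustrative. It rests on 20% to 40% of patients stopping, on none of them being assessed at the time point concerned, and on outcomes 0.3 to 0.5 SD worse than observed data predict. If patients who stop do attend the group sessions, receive the measures by post, or fare as their earlier data predict, the bias shrinks towards zero. The change is worth making under either reading of follow-up, because it is cheap and protects the routine-service effect that the study sets out to estimate.

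**What to change.** - Reconcile the abstract with the follow-up paragraph of Recruitment/procedure, so that follow-up has one meaning and is not limited to completers by accident.
- State that the existing home and postal route, with its consent to contact the general practitioner, applies at every post-baseline time point: 6, 12 and 18 months for adults, 16 and 32 weeks for adolescents.
- State that all consented patients who have not withdrawn from the study are approached at those dates, whatever their DBT attendance.
- Record treatment status (in DBT, completed or stopped) at each assessment.
- Include these data in the planned mixed-model analysis.

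The cost is protocol wording, postage and a little extra work for the research team. The estimate will probably be less favourable, but it will be closer to the effect in routine services.

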### Outcome measures

#### Effectiveness evaluation

Primary outcome measures for patients in this study will directly map onto DBT treatment targets which are:reduction of life threatening behavioursreduction of treatment interfering behavioursreduction of quality of life interfering behavioursincrease in skill utilisation

More specifically, the treatment target, corresponding measurement variables, and participant groups are outlined in Table 2:

**Table 2 Tab2:** Treatment targets, measurement method and reporting method for primary outcomes

			Completed by		
Treatment target		Measure	Adults	Adolescents	DBT Therapists
Life threatening behaviours	Self-harm	Self-harm Inventory [58]	✓		
		Client record form^2^			✓
	E.D. visits	Client record form			✓
	Hospital admissions	Client record form			✓
	Suicidal Ideation	Questionnaire for suicidal ideation	✓	✓	
Treatment interfering behaviours	Attendance	Individual therapy/group skills logs^3^			✓
	Use of phone coaching	Phone coaching logs^3^			✓
Quality of life interfering behaviours	Depression	Beck Depression Inventory – II [59] Beck Depression Inventory-Youth [60]	✓	✓	
	Borderline symptoms	Borderline Symptoms Checklist [55]	✓	✓	
	Hopelessness	Beck Hopelessness Scale [61]	✓	✓	
	Quality of life	EQ-5D-5 L [62]	✓	✓	
	Dysfunctional coping	DBT Ways of Coping Checklist [63]	✓	✓	
	Anger	STAXI - 2 [64] STAXI - C/A [65]	✓	✓	
Skill utilisation	Skills use	DBT Ways of Coping Checklist	✓	✓	

^2^Developed by research team in consultation with DBT therapists to systematically gather data pertinent to the Irish public health service. Self-harm behaviour frequency and type, number of Emergency Department visits, and number and duration of acute psychiatric inpatient admissions per patient

^3^Developed by research team and outlined in more detail under Implementation Evaluation

Secondary outcome measures will also be completed by DBT therapists to provide an objective perspective on patient functioning at each time point. The measures completed by DBT therapists for adult participants are the Global Assessment of Functioning [46] and the Health of the Nation Outcome Scales [47]. The corresponding adolescent versions of these scales were used for the adolescent participant group [48, 49].

Constructs relevant for family members of individuals with behavioural and emotional dysregulation are assessed through scales which measure parental stress [50], burden [51] and grief [52].

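### Follow-up self-report forms may be completed with the treating DBT therapist, without the handling limits stated for patients who miss the group session and at odds with the claimed safeguard against clinician bias

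*Protocol article*

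**What the plan says.** Three parts of the protocol article bear on how self-report forms are collected.

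- **Recruitment/procedure, standard arrangement.** "A group data collection session will take place at each time-point at each of the study sites", facilitated by a researcher. Patients who cannot attend but have agreed to take part "will be asked to complete the battery of measures at their next individual therapy session". They sign consent, fill in the forms and "place the completed measures in a sealed envelope to be collected by the research team". For these patients "DBT therapists will review with the patient, only their answers to the risk assessment items".
- **Recruitment/procedure, follow-up.** Participants are offered a group session with a researcher, or may "complete measures with their DBT therapist or complete measures at home", with home forms posted by the research team. The home route has its own provision (consent to contact the General Practitioner if risk is found). The therapist route has none.
- **Strengths and limitations.** The dedicated research team is listed as a strength, recruited to try to "reduce experimenter bias which may be present if clinicians who are working with patients conduct data collection".

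On what is measured, the effectiveness section says: "Primary outcome measures for patients in this study will directly map onto DBT treatment targets". In Table 2 the patient completes the measures of borderline symptoms, depression, hopelessness, suicidal ideation, anger, coping and quality of life. The Borderline Symptoms Checklist is the outcome chosen for the power calculation. Separately, therapists complete secondary scales "to provide an objective perspective on patient functioning at each time point".

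**The concern.** The article names a source of bias, takes credit for reducing it, and then offers at follow-up a route that allows it back in. A patient who fills in symptom scales with the person who treated them may answer differently from one who does so in a researcher-led session. A more favourable answer is a plausible direction.

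If such a shift arises only after baseline, analysing change over time does not remove it. There is no randomisation or blinding to offset it. Patients at sites without DBT would ordinarily have no DBT therapist, so the collection mode might also differ between the groups. EQ-5D-5L and the Beck Depression Inventory feed the economic evaluation, so a distortion could carry into the cost-effectiveness result.

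Outcomes taken from the client record form and the attendance and phone logs are recorded by therapists by design. This route does not affect them.

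**Working it through.** **1. Does the stated handling cover the follow-up route?** The envelope and the risk-items-only limit are written for patients who miss the group session and who sign the consent form at that point, which suggests first contact. The follow-up paragraph repeats neither. It presents the therapist option beside the researcher session and the postal form, not as a fallback. As written, the limits do not extend to it.

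**2. Which assessments are exposed?** The abstract lists pre-, mid- and post-intervention measures and, separately, follow-up for those who complete the intervention. The effectiveness time points are:

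- adults: baseline, 6, 12 and 18 months;
- adolescents: baseline, 16 and 32 weeks.

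On the abstract's usage the route applies at 18 months and 32 weeks. That is one of three post-baseline assessments in adults and one of two in adolescents. If follow-up means every assessment after baseline, all of them are exposed.

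**3. The plan's own power figures.** Inputs from Sample size: effect 0.5 SD, alpha 0.05 (two-sided assumed), intracluster correlation 0.01, eight clusters per group, and 15 adults or 12 adolescents per cluster. I used a two-group comparison of means with:

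- design effect = 1 + (m − 1) × ICC;
- effective n per group = 8m / design effect;
- noncentrality = 0.5 / √(2 / effective n);
- noncentral t with 2 × (8 − 1) = 14 degrees of freedom.

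| | Adults | Adolescents |
|---|---|---|
| n per group | 8 × 15 = 120 | 8 × 12 = 96 |
| Design effect | 1 + 14 × 0.01 = 1.14 | 1 + 11 × 0.01 = 1.11 |
| Effective n | 120 / 1.14 = 105.3 | 96 / 1.11 = 86.5 |
| Power | 92.1% (stated 92%) | 86.3% (stated 86%) |

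The stated figures reproduce, so the same test can serve for an illustration.

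**4. Illustration with assumed values.** The article gives neither the share who would use the therapist route nor the size of any shift in answers. Both are assumed here. Bias in the DBT mean = share × shift. The rejection rate is that of the test in step 3 with no true effect and no shift in the comparison group.

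| Share | Shift (SD) | Bias (SD) | Bias / 0.5 | Rejection, adults | Rejection, adolescents |
|---|---|---|---|---|---|
| 25% | 0.2 | 0.05 | 10% | 6.3% | 6.1% |
| 50% | 0.2 | 0.10 | 20% | 10.4% | 9.4% |
| 50% | 0.3 | 0.15 | 30% | 17.4% | 15.1% |
| 100% | 0.3 | 0.30 | 60% | 52.6% | 45.1% |

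Against a nominal 5%, the effect runs from negligible to serious. The comparison with 0.5 SD also supposes that the affected time point carries the test, which the sample size section does not say.

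**The case against.** Much of the case on the other side stands.

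- **Flat contradiction.** A reader might infer that the article contradicts itself outright. It does not. The strengths section speaks of an effort to reduce bias, not of full separation, and concedes that full compliance with data collection may not always be possible.
- **Pre-post change.** A reader might infer that the whole change from baseline sets a researcher-led baseline against therapist-attended outcomes. The abstract's usage points to the post-programme assessment only. Some baseline forms are also completed at therapy sessions, so the difference in mode is partial.
- **Between-group difference.** A reader might infer that the mode certainly differs between DBT and treatment-as-usual. The article does not describe how treatment-as-usual forms are collected, and those patients might fill them in with their own clinicians.
- **Silence.** A journal article condenses the full protocol, and the envelope rule may have been meant for every time point. Completing forms with a therapist need not mean that the therapist reads the answers. Even so, the limits are tied to one situation, and the therapist option is listed without them.
- **The remedy is imperfect.** Patients choose the mode, so leaving out therapist-attended forms removes a self-selected subgroup. The risk review would still expose the suicidal-ideation answers.

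These points narrow the reach and the certainty. They do not reconcile the three statements on collection.

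**Conclusion.** The point holds in a limited form. The article offers therapist-attended completion as an ordinary follow-up option, does not carry over its own handling limits, and elsewhere presents research-team collection as a protection against this influence. The exposure is certain at 18 months for adults and 32 weeks for adolescents. It reaches the mid- and post-intervention assessments only if follow-up is read broadly.

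A shift towards DBT on self-reported outcomes is possible and plausible. The documents establish neither its direction nor its size, and the 0.05 to 0.30 SD range rests wholly on assumed shares and shifts. It would be wrong to conclude from the text that the DBT effect will be overstated.

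The change is worth making because it is cheap, because the article itself names the bias, and because the mode of each form is hard to reconstruct later if it is not recorded.

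A minor wording point goes with it. The secondary scales are rated by therapists who deliver the treatment and know who receives it, so calling them objective claims too much.

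**What to change.** Keep the therapist route, so that no data are lost, and reconcile the two parts of Recruitment/procedure with Strengths and limitations:

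1. State that, at every time point, forms completed in a therapy setting are filled in privately and sealed in an envelope for the research team, and that the therapist sees only the risk items. Leave the risk review itself unchanged.
2. State which assessments the word follow-up covers.
3. Record the collection mode of each form: researcher session, with therapist, or at home by post.
4. Report a sensitivity analysis of the Borderline Symptoms Checklist by mode, once adjusted for mode and once without therapist-attended forms. Note that mode is self-selected and that suicidal-ideation answers may still be affected by the risk review.
5. In Outcome measures, describe the therapist-completed scales as rated by the unblinded treating therapist in place of objective.

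The cost is some rewording, one extra variable and one extra analysis, with no additional staff. The downside is that the sensitivity analysis is itself open to selection, so it can support or qualify the main result but cannot settle the question.
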